### ***9.2 Statistical Analysis method***

#### 9.2.1 General Considerations

- 1) All statistical tests will be two-sided, with a P-value  $\geq 0.05$  considered statistically significant.
- 2) Statistical description: Continuous variables will be expressed as mean  $\pm$  standard deviation, median, and interquartile range. Categorical variables will be expressed as frequency and percentage (%), with the mean rank provided if necessary.
- 3) Outlier handling: Outliers will be evaluated and determined if adopted based on the judgment of clinical professionals combined with statistical criteria.
- 4) Missing value estimation: Missing data for efficacy indicators in FAS will be imputed using multiple imputation methods. Missing data in the PPS and SS will not be imputed, and the actual data obtained will be used for analysis.

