### **3.4 Sample size calculation**

The sample size is calculated based on the estimated post-treatment CT-FFR values. The PROMISE study revealed an average CT-FFR value of  $0.77 \pm 0.1$  for patients with ICL. A clinical study indicated that after traditional Chinese medicine intervention, patients with CAD had CT-FFR values of  $0.92 \pm 0.16$ . Therefore, it was assumed that the CT-FFR value in the control group is 0.77 and the value in the intervention group could be elevated to 0.92 after treatment, the standard deviation  $\sigma = 0.13$  for both two groups. Results from the NXT study indicated that for every 0.05 unit decrease in CT-FFR, there was an independent correlation with the increasing rate of composite cardiovascular events. Based on this, we have set the cut-off value  $\Delta=0.03$  in this superiority trial. The number of cases in the two groups is arranged in a ratio of 1:1, so  $c=1$ . Given a type I error rate of  $\alpha = 0.05$  (two-side test), a power of 95% (type II error rate of  $\beta = 0.05$ ), so  $u_\alpha=1.96$ ,  $u_\beta=1.64$ ,  $n_1=n_2\approx 55$ . Considering the maximum dropout rate of 10%, a total of 120 patients is needed. The calculation formula is as follows:

$$n_1 = \left(\frac{1+c}{c}\right) \left[\frac{(u_\alpha + u_\beta) \sigma}{\mu_T - \mu_C - \Delta}\right]^2 + \frac{1}{4} u_\alpha^2, \text{ and } n_2 = c n_1$$

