## **9. Statistical Analysis**

All statistical tests will be conducted as two-tailed tests, and a P-value  $\leq 0.05$  will be considered statistically significant for the tested differences.

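### Section 9.2.1 calls P ≥ 0.05 statistically significant, the reverse of section 9 and of the alpha used to size the trial

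*Protocol*

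**What the plan says.** Section 9 of the protocol opens with a rule for all tests: they are two-tailed, "a P-value $\leq 0.05$ will be considered statistically significant for the tested differences".

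Section 9.2.1, item 1, then gives a second rule of the same scope: every test is two-sided, "with a P-value $\geq 0.05$ considered statistically significant".

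Two other places bear on which rule is meant. Section 3.4 sizes the trial for a two-sided type I error rate of 0.05, with a critical value of 1.96. Section 9.2.2 specifies 95% confidence intervals for the primary outcome, the secondary efficacy outcomes and the MACE hazard ratio.

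**The concern.** The two sentences use the same cut-off with opposite inequality signs. Each claims to govern all tests, and the protocol neither reconciles them nor gives one precedence. As written, section 9.2.1 turns the decision rule upside down: no evidence of a difference counts as significant, and strong evidence does not.

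The sentence is not confined to a side analysis. It covers the primary CT-FFR comparison, every secondary efficacy outcome, the Cox model for MACE and the subgroup analyses. It also stands under the general considerations of the methods subsection, which is where someone writing a detailed analysis plan or the analysis programs would look for the threshold and might copy it.

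**Working it through.** **1. The two rules side by side**

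| Place in the protocol | Scope | Significant when |
|---|---|---|
| Section 9 | all tests, two-tailed | P ≤ 0.05 |
| Section 9.2.1, item 1 | all tests, two-sided | P ≥ 0.05 |

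The only P-value on which they agree is exactly 0.05.

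**2. Which rule matches the rest of the protocol**

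Section 3.4 gives α = 0.05 (two-sided) and u_α = 1.96. The protocol's own figure reproduces:

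2 × (1 − Φ(1.96)) = 0.0500

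This is the error rate of a test that rejects when P ≤ 0.05. The 95% intervals in section 9.2.2 correspond to the same rule. Section 9 therefore fits both places and section 9.2.1 fits neither.

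**3. The section 9.2.1 rule under the null**

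With no true difference, P is uniform on 0 to 1:

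- Section 9: Pr(P ≤ 0.05) = 0.05
- Section 9.2.1: Pr(P ≥ 0.05) = 1 − 0.05 = 0.95

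**4. The section 9.2.1 rule at the planned effect**

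Inputs from section 3.4: means of 0.77 and 0.92, margin 0.03, SD 0.13 in each group, about 55 per arm.

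- Net difference: 0.92 − 0.77 − 0.03 = 0.12
- Standard error: 0.13 × √(2/55) = 0.0248
- Standardised difference: 0.12 / 0.0248 = 4.84
- Pr(P ≤ 0.05) = Φ(4.84 − 1.96) = Φ(2.88) = 0.998
- Pr(P ≥ 0.05) = 1 − 0.998 = 0.002

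Variations on these inputs:

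- With 54 per arm (120 less 10% dropout is 108, or 54 each), Φ(4.80 − 1.96) = Φ(2.84), again about 0.998.
- With the full difference of 0.15 and 55 per arm, Pr(P ≤ 0.05) is above 0.9999.

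**5. Why step 4 gives 99.8% and not the 95% stated**

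The 55 per arm is taken here as printed. The formula in section 3.4 with its own inputs gives 2 × [(1.96 + 1.64) × 0.13 / 0.12]² + 1.96²/4 = 30.42 + 0.96 = 31.4, or 32 per arm, at which power is 0.958. That is a separate matter. With 32 per arm the section 9.2.1 rule would still label a true effect significant only 1 − 0.958 = 4.2% of the time.

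**The case against.** The strongest reply is that the intent is not in doubt. Section 9 has the conventional rule, section 3.4 and the 95% intervals agree with it, and one character in section 9.2.1 stands against them. No competent analyst would follow that character while printing 95% intervals beside the P-values. On this view the 95% false-positive figure describes something that will not happen, and the point is an editorial correction. The statistical analysis plan, which is not at hand, may also state the rule correctly.

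Much of this stands. It is almost certainly a slip, the intended rule can be recovered from the protocol alone, and no sample size, model or estimand depends on it. The percentages illustrate the literal rule and do not estimate the risk to this trial. What does not follow is that the text can stay. The sentence sets the criterion by which the primary analysis becomes a conclusion, and a protocol with two opposite criteria has no unambiguous prespecified one. A correct analysis plan would not remove the error from the protocol.

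A misread sign in the conversion from PDF cannot be fully excluded. However, the same conversion gave the correct sign in section 9 and plausible signs in the exclusion criteria (section 2.3), so nothing points to an artefact. A glance at the source file would settle it.

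**Conclusion.** The concern holds. Section 9.2.1 item 1 contradicts section 9 and is incompatible with the two-sided alpha of 0.05 in section 3.4. Taken literally it raises the false-positive rate from 5% to 95%, and at the planned effect it reduces the chance of calling a real benefit significant from about 99.8% to about 0.2%. The null figure needs only a valid test, so that P is uniform. The figures at the planned effect rest on the section 3.4 means, margin and SD, 55 per arm and a normal approximation. This must be corrected because it is the decision rule for every test, even though literal application is unlikely.

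**What to change.** In section 9.2.1 item 1, change the sign so that two-sided P ≤ 0.05 is significant, as in section 9. Better, delete the threshold from one of the two sections so that it is stated once, and check that the statistical analysis plan carries the same rule. The cost is one character or one deleted sentence, with no effect on sample size, power, analysis models, data collection or patients.

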#### 9.2.2 Efficacy Analysis

- 1) Primary Efficacy Outcome: CT-FFR.
  - Description: CT-FFR values of the target vessels at baseline and 6 months after

treatment, as well as the difference from baseline to 6-month will be described. For multiple vessel lesions, the CT-FFR value of the most severely narrowed vessel will be selected.

- Intergroup Comparison: A linear mixed model will be used for comparison between groups. The dependent variable is the difference in CT-FFR from baseline to 6-month. Fixed effects include group and center, while random effects include subjects. Covariates include baseline values of CT-FFR, age, gender, BMI, systolic blood pressure, diastolic blood pressure, LDL-C, FBG, smoking status, alcohol consumption, family history of early-onset cardiovascular disease, presence of cerebrovascular disease, peripheral vascular disease, diabetes mellitus, hypertension, dyslipidemia, and concomitant use of PCSK-9 inhibitors.
  - Estimation: The least squares method will be used to estimate mean differences and 95% confidence intervals (CI).
- 2) Secondary Efficacy Outcomes
- a) Coronary imaging assessment indicators
- Description: %DS measurement will use the most narrowed location as the result; CACS and Gensini scores will use the total score as the result. Values of %DS, CACS, and Gensini scores at baseline and 6 months after treatment, as well as the difference from baseline to 6-month will be described.
  - Intergroup Comparison. A linear mixed model will be used, with the dependent variable being the difference from baseline to 6-month. Fixed effects include group and center, random effects include subjects, and covariates include baseline values.
  - Estimation: The least squares method will be used to estimate the mean difference and 95% CI.
- b) SAQ score
- Description: SAQ scores at baseline, 2, 4, and 6 months after treatment will be described, along with the differences from baseline to 2, 4, and 6 months.
  - Intergroup Comparisons: A mixed model for repeated measures will be used, with the dependent variable being the difference in SAQ scores at 2, 4, and 6 months relative to baseline, with the primary assessment time point at 6 months after treatment. Fixed effects include group and center, random effects include subjects. Covariates include baseline SAQ scores, visit times, the interactions between baseline and visit, and the interactions between treatment group and visit.
  - Estimation: The least squares method will be used to estimate the mean difference between groups and the 95% CI.
- c) Serum inflammatory factors, blood lipids, and carotid ultrasound indicators
- Description: Values at baseline and 6 months after treatment, as well as the difference from baseline to 6-month will be described.
  - Intergroup Comparisons: A linear mixed model will be used, with the dependent variable being the difference from baseline to 6-month. Fixed effects include group and center, and random effects include the subjects, with baseline values as covariates.

- Estimation: The least squares method will be used to estimate the mean difference and 95% CI.
- 3) Endpoint Event: MACE
- Description: The incidence rate of MACE from baseline to the 1-year follow-up will be described.
  - Intergroup Comparisons: The Cox proportional hazards model will be used, with the dependent variable being the occurrence of MACE and the survival time variable being the time from baseline to either the occurrence of MACE or the end of follow-up. The primary independent variable is the group. Covariates include age, gender, BMI, systolic blood pressure, diastolic blood pressure, LDL-C, FBG, smoking status, alcohol consumption, family history of early-onset cardiovascular disease, presence of cerebrovascular disease, peripheral vascular disease, diabetes mellitus, hypertension, dyslipidemia, concomitant use of PCSK-9 inhibitors, and study center.
  - Estimation: The partial likelihood method will be used to estimate the hazard ratio and its 95% CI.
- 4) Subgroup analyses: Considering the significant impact of concomitant diabetes and the use of PCSK-9 inhibitors on drug efficacy, subgroup analysis of the primary efficacy outcome and endpoint events will be performed in SCAD patients with diabetes and SCAD patients with the use of PCSK-9.

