## **1. Study objective**

To evaluate the efficacy and safety of Qing-Xin-Jie-Yu Granules (QXJYG) for intermediate coronary lesions (ICL) in patients with stable coronary artery disease (SCAD).

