### **2.2 Inclusion criteria**

- 1) Patients with SCAD who have at least one major coronary artery with luminal diameter stenosis of 50% to 70% confirmed by coronary computed tomography angiography (CCTA).
- 2) Heart function grade NYHA grade I - II.
- 3) Patients aged 18 to 75 years.
- 4) Patients who are informed and voluntarily sign the ICF.

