### **2.3 Exclusion criteria**

- 1) Patients have previously undergone coronary stent implantation, coronary artery bypass grafting or MI within three months.
- 2) Lesions with diameter stenosis  $\geq 50\%$  in the left main coronary artery or in all three major arteries.
- 3) Diffuse lesions throughout the diseased vessels.
- 4) Severe blood pressure fluctuations or difficult-to-control hypertension with systolic blood pressure  $\geq 160\text{mmHg}$  and diastolic blood pressure  $\geq 100\text{mmHg}$  in the past 3 months.
- 5) Resting heart rate  $> 100$  beats/min and difficult to control.
- 6) Patients have previously undergone other cardiac operations, such as valve replacement.
- 7) Patients with severe cardiac, hepatic or renal insufficiency that are unsuitable for CCTA and related examination and treatment.
- 8) Patients suffering from mental disorders.
- 9) Patients suffering from hepatitis, tuberculosis, AIDS, or other infectious diseases.
- 10) Allergic sufferers.
- 11) Pregnant and lactating women
- 12) Life expectancy is less than one year.
- 13) Participation in other clinical trials within the last three months.

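### The primary CT-FFR is read in the most severely narrowed vessel, which the entry criteria allow to be a lesion above 70%, and the target vessel is neither defined nor tied to the baseline scan

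*Protocol*

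**What the plan says.** Section 1 states the aim as evaluating the granules "for intermediate coronary lesions (ICL) in patients with stable coronary artery disease (SCAD").

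Section 2.2 admits patients with "at least one major coronary artery with luminal diameter stenosis of 50% to 70" per cent on CCTA. Section 2.3 excludes stenosis of 50% or more "in the left main coronary artery or in all three major arteries", and separately "Diffuse lesions throughout the diseased vessels". Neither section sets an upper limit on stenosis in the arteries other than the qualifying one.

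Section 9.2.2(1) describes "CT-FFR values of the target vessels at baseline and 6 months after" treatment, and then gives the rule for patients with more than one lesion: "For multiple vessel lesions, the CT-FFR value of the most severely narrowed vessel will be selected". For the model, "The dependent variable is the difference in CT-FFR from baseline to 6-month".

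For the stenosis outcome in section 9.2.2(2), %"DS measurement will use the most narrowed location as the result". The flow chart in section 12 schedules both CT-FFR and CCTA at baseline and month 6.

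**The concern.** The trial is about intermediate lesions, and a patient enters because one artery carries such a lesion. The endpoint rule follows the tightest vessel, which need not be the qualifying one. Where the two differ, the primary value describes a different kind of lesion, and the qualifying lesion does not contribute to the primary analysis at all.

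There is also a second, weaker point. A change from baseline is interpretable only if the same vessel is read twice. The term *target vessel* is not defined anywhere in the protocol, and the selection rule names no scan. Stenosis is measured again at month 6, so someone applying the rule literally at each scan could subtract one artery's CT-FFR from another's. The %DS rule has the same gap.

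What is at stake is the meaning of the primary result in patients with multi-vessel disease: which lesion the estimated effect refers to.

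**Working it through.** **Step 1. Can the measured vessel be non-intermediate?** Take a patient with a 60% stenosis in one major artery, a focal 80% stenosis in a second, and neither the left main nor the third artery at 50% or more.

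| Provision | Applied to this patient |
|---|---|
| 2.2(1): one major artery at 50–70% | Met by the 60% artery |
| 2.3(2): left main at 50% or more | Does not apply |
| 2.3(2): all three major arteries at 50% or more | Does not apply; only two are |
| 2.3(3): diffuse lesions | Does not apply; the lesions are focal |
| 9.2.2(1): tightest vessel is used | Selects the 80% artery |

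The patient meets the lesion criteria, and the primary value comes from outside the 50–70% range. This needs a second lesion **above 70%**. If both arteries lie within 50–70%, the rule picks the tighter of two intermediate lesions and there is no mismatch with section 1. Patients with a single diseased vessel are unaffected. The planning assumption in section 3.4 also concerns intermediate lesions: its control mean of 0.77 is taken from such patients.

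**Step 2. Is the vessel fixed in time?** Section 9.2.2 refers to target vessels at both visits, which suggests the same vessel twice. It does not say so, and the ranking rule names neither a scan nor a stenosis measure (diameter or area). Re-ranking at month 6 is therefore not excluded.

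**Step 3. How much could dilution matter?** The inputs from section 3.4 are means of 0.77 and 0.92 (difference 0.15), SD 0.13, margin 0.03, two-sided α of 0.05, and about 55 per group.

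The plan's own figure comes first. Its formula gives 2 × [(1.96 + 1.64) × 0.13 / 0.12]² + 1.96²/4 = 30.42 + 0.96 = 31.4, that is 32 per group, so the stated 55 is not reproduced. That is a separate matter. It is relevant here only because the power below is calculated at the stated 55.

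Suppose a share *p* of patients contributes a vessel in which treatment has no effect at all. Both *p* and the complete absence of effect are assumptions. The difference becomes 0.15(1 − *p*), the standard error is 0.13 × √(2/55) = 0.0248, and power = Φ[(0.15(1 − *p*) − 0.03)/0.0248 − 1.96].

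| *p* (assumed) | Difference | Power at 55 per group |
|---|---|---|
| 0 | 0.150 | 99.8% |
| 10% | 0.135 | 98.9% |
| 20% | 0.120 | 95.3% |
| 30% | 0.105 | 85.7% |

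**Step 4. How often would vessels switch if they were re-ranked?** I simulated 400,000 patients with two diseased vessels, true %DS uniform on 50–70, independent reading errors at each scan, and no true change. With an assumed error SD of 2.5, 5 or 7.5 points, the narrowest vessel differs between scans in 17%, 30% or 37% of these patients. The rates apply only to two-vessel patients, and only if re-ranking is done. They describe stenosis ranking and do not translate directly into CT-FFR error.

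**The case against.** The strongest reply is that the selection rule should be read with the sentence before it. In a trial of intermediate lesions, the target vessels are naturally those carrying a qualifying lesion, and the rule only chooses among them; a vessel above 70% would then never be selected. Section 2.1 also leaves the diagnosis of intermediate lesions to an outside guideline. This reading is possible, but the protocol does not state it: the term is undefined, and taken literally the rule covers all of the patient's lesions. The ambiguity stands.

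On timing the reply is better. A change in a target vessel ordinarily means the same vessel twice, and vessel matching is often left to an SAP or imaging manual. I accept that the same vessel is probably intended; what remains is unanchored wording. The choice of lesion is different, because the protocol itself states that rule, and an SAP that followed it would inherit the mismatch.

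It can also be said that the patient's worst vessel is a coherent patient-level endpoint. It is, but it is not the one that section 1 describes.

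A reader might go further and infer that choosing the extreme vessel damages the endpoint through regression to the mean. The check does not support this as an argument against the rule. In the Step 4 simulation the mean change in %DS with no true effect is about 0 when the narrowest vessel is re-selected at each scan, and −0.5, −1.8 or −3.3 points when it is fixed at baseline. Fixing the vessel therefore does not remove regression to the mean. In a randomised, blinded comparison it is equal in both arms in expectation, and baseline CT-FFR is already a covariate.

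**Conclusion.** The point holds, and it should be fixed. As written, the rule can take the primary CT-FFR from a lesion above 70%, which does not match the stated objective, and it leaves the vessel unanchored between scans. The first part follows from sections 1, 2.2, 2.3 and 9.2.2 read together, provided that the target vessel is not silently restricted to the qualifying artery. The second is a gap in wording, not evidence that different vessels will be compared.

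The consequence is a blurred estimand and possible dilution, confined to patients with more than one diseased vessel. The documents do not give their share, nor the share with a second lesion above 70%, so no count of affected patients can be given. An assumed percentage of the 120 patients would illustrate the effect but would not be evidence of its size. On the stated 55 per group, loss of power is modest unless a large share of patients contributes a vessel with no effect at all.

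Two stronger readings are not supported. Not every patient with a second, tighter lesion is affected; only those in whom it exceeds 70% have the mismatch. Nor is bias between arms shown: a rule applied blind and identically in both groups mainly adds noise and changes what the estimate refers to.

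**What to change.** In section 9.2.2(1), define the target vessel from the baseline CCTA as the major artery with the qualifying 50–70% stenosis and, if there is more than one, the narrowest within that range. Name the stenosis measure used for the ranking. Record the vessel and segment before randomisation. State that CT-FFR is measured in the same vessel, and %DS and %AS at the same lesion, at month 6. CT-FFR in the patient's worst vessel can be kept as a supplementary analysis.

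The cost is a sentence or two in section 9.2.2 and one entry on the case report form, with no extra imaging. The downside is that vessels above 70% no longer supply the primary value. If the investigators do want the worst vessel as the primary measure, the objective should say so, and the vessel should still be fixed from the baseline scan.

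### The random subject effect is redundant and unidentifiable for CT-FFR and every other outcome with one post-baseline value; separately, PCSK-9 inhibitor use has no clear time point

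*Protocol*

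**What the plan says.** Protocol section 9.2.2 analyses the primary outcome with a linear mixed model. "The dependent variable is the difference in CT-FFR from baseline to 6-month", and "Fixed effects include group and center, while random effects include subjects". CT-FFR is described at baseline and month 6 only, and the flow chart in section 12 schedules it at visits 1 and 4 only. Where several vessels are diseased, one is used: "For multiple vessel lesions, the CT-FFR value of the most severely narrowed vessel will be selected". Estimation of the mean difference and its confidence interval is said to be by least squares.

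The secondary outcomes measured once after baseline have the same structure. For inflammatory factors, lipids and carotid ultrasound the text reads "Fixed effects include group and center, and random effects include the subjects, with baseline values as covariates", and the coronary imaging measures are treated alike. Only SAQ, recorded at months 2, 4 and 6, has repeated post-baseline values.

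The primary covariate list opens "Covariates include baseline values of CT-FFR, age, gender, BMI" and ends "hypertension, dyslipidemia, and concomitant use of PCSK-9 inhibitors". The Cox model for MACE also adjusts for concomitant PCSK-9 inhibitor use, but its list has no baseline qualifier. The subgroup analyses, justified by the impact of diabetes and PCSK-9 inhibitors on drug efficacy, are to be done in "SCAD patients with diabetes and SCAD patients with the use of PCSK-9". The flow chart records concomitant medication at baseline and at months 2, 4 and 6.

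**The concern.** A random subject effect separates variation between subjects from variation within them, which needs at least two outcome values for some subjects. Here nobody has two, so the subject term and the residual are the same quantity under two names. Software that fits the model must divide one variance into two parts without information, and a degrees-of-freedom rule based on what remains after the fixed and random parts has nothing left. The primary test should not depend on how a program handles that.

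The second matter is independent of the first. If PCSK-9 inhibitor use means use at any time up to month 6, the covariate and the subgroup can be affected by treatment. Adjusting for such a variable changes the effect being estimated, and subgroups formed on it are no longer protected by randomisation. In addition, an analysis confined to diabetics and users gives an effect within each of those groups, but cannot show whether that effect differs from the one in the other patients, which is the reason the protocol gives for the subgroups.

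**Working it through.** **Inputs.** From the protocol: 120 patients with at most 10% dropout (section 3.4), so 120 × 0.90 = 108 evaluable; three centres (3.1); two groups; one vessel and one change value per subject (9.2.2, 12); planned CT-FFR difference 0.92 − 0.77 = 0.15 (3.4). The protocol gives no figure for this point to reproduce.

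**Variance structure.** With one value per subject the random-effect design matrix Z is the identity, so

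Var(y) = σ²_subject · ZZ′ + σ²_residual · I = (σ²_subject + σ²_residual) · I.

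The likelihood depends on the two variances only through their sum.
- Simulated data, N = 108: the REML log-likelihood was 143.914451 with the subject effect taking 0, 25, 50, 75 or 99% of the variance.
- Second simulation, N = 110: it was 156.4203 at 0, 25, 50 and 75%. A mixed-model routine converged under three optimisers, but split the variance 0.0077/0.0077 under two of them and 0.0126/0.0029 under the third.

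Multiple imputation (9.2.1) does not change this, because each completed data set still holds one value per subject.

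**Treatment estimate.** Since Var(y) is a multiple of I, generalised least squares reduces to ordinary least squares. Mixed model and ANCOVA agreed in both simulations: 0.0563 (SE 0.02735) with N = 108, and 0.0755 (SE 0.0240) with N = 110.

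**Degrees of freedom.** Count one parameter per covariate: intercept 1, group 1, centre 2, and 17 covariates (baseline CT-FFR, age, gender, BMI, two blood pressures, LDL-C, FBG, smoking, alcohol, family history, cerebrovascular disease, peripheral vascular disease, diabetes, hypertension, dyslipidaemia, PCSK-9 inhibitor), 21 in all.
- ANCOVA: 108 − 21 = 87.
- Model as written: rank[X Z] = 108, so 108 − 108 = 0.

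With t = 0.0563 / 0.02735 = 2.06, P is 0.040 on the normal distribution, 0.043 on 87 df, and undefined on 0 df.

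**PCSK-9 inhibitor use.** The texts side by side:
- Primary model: the words on baseline values may govern CT-FFR alone or the whole list.
- Cox model: no such words.
- Subgroup: no time point.
- Flow chart: concomitant medication recorded through month 6.

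If use started after randomisation differs by arm, the adjusted and total effects differ by (imbalance in use) × (effect of the drug on CT-FFR). Both factors are assumptions:

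| Use by arm | Imbalance | Assumed effect | Shift |
|---|---|---|---|
| equal | 0 | any | 0 |
| 20% vs 10% | 0.10 | 0.03 | 0.003 |
| 20% vs 10% | 0.10 | 0.05 | 0.005 |
| 30% vs 10% | 0.20 | 0.05 | 0.010 |

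Simulation agreed: with an effect of 0.05, total and adjusted estimates were 0.0454 and 0.0505 at 20% vs 10%, and 0.0407 and 0.0505 at 30% vs 10%. Against the planned 0.15, shifts of 0.005 and 0.010 are 3% and 7%.

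**The case against.** The strongest reply is that the superfluous term is harmless. The model converges, the estimate and standard error are those of ANCOVA, and the arbitrary variance split would not be reported. The least-squares statement already points to ANCOVA. A rule returning 0 df would fail visibly, and the choice of df method is commonly left to an SAP. Most of this stands. A reader might infer that the model cannot be fitted, or that the primary result is unreliable; the calculations contradict both, and the P-values on the two usable references differ only by 0.003. What does not fall away is that the protocol itself states a random effect its data cannot support, for the primary outcome and several secondary ones. That is a stated error, not a detail left for later.

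On PCSK-9 inhibitors, the other items in the primary list are baseline characteristics. The protocol also uses the word concomitant of diabetes, where it means co-existing, and medication history is collected at baseline. Lipids are scheduled only at baseline and month 6, so no protocol LDL-C result between those visits would prompt prescribing. These are fair points. A reader might infer that the protocol adjusts for use after randomisation; the text does not establish that. It leaves the time point open, most clearly in the Cox list and the subgroup.

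Interaction tests are often left to an SAP. Here, however, the protocol names the groups to be analysed and gives effect modification as the reason, so the stated analysis does not match its stated purpose.

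**Conclusion.** The point holds as an error of specification with small numerical consequences. For CT-FFR, the CCTA measures, inflammatory factors, lipids and carotid ultrasound, the random subject effect is redundant and unidentifiable. The group estimate and standard error are unaffected; the only open element is the reference distribution, with 0 df under one reading of the written model and 87 under ANCOVA (assuming 108 evaluable patients and one parameter per covariate).

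The PCSK-9 point is a separate ambiguity. It has no bearing on whether the model can be fitted, and it is not evidence that the randomised comparison is compromised. Its likely size is 0.005 to 0.010 in CT-FFR under an assumed 10 to 20 point imbalance and an assumed effect of 0.05, less with a smaller effect, and zero if use is equal by arm. Both matters should be corrected, since the correction loses nothing.

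**What to change.** In section 9.2.2:

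1. For CT-FFR, the CCTA measures, inflammatory factors, lipids and carotid ultrasound, replace the linear mixed model by ANCOVA of the change, with group, centre and the baseline value, plus the listed baseline covariates for CT-FFR, and no random subject term. Keep the repeated-measures model for SAQ only.
2. In the primary and Cox covariate lists and in the subgroup definition, define PCSK-9 inhibitor use as status at randomisation.
3. Assess the diabetes and PCSK-9 subgroups by a group-by-factor interaction in the whole FAS, and report the treatment effect at both levels of each factor.

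The cost is wording only. Medication is already recorded at baseline, no patient or visit is added, and the treatment estimate and its standard error are the same with or without the random term.
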